**Interim analyses {21b}**

No interim analysis will be conducted.

**Methods for additional analyses (e.g., subgroup analyses) {20b}**

Further analysis will investigate if the effect of PrEP varies depending on the factors used for stratification.

**Methods in analysis to handle protocol non-adherence and any statistical methods to handle missing data {20c}**

Non-compliance issues will be investigated by estimating the local average treatment effect (LATE).

**Plans to give access to the full protocol, participant-level data and statistical code {31c}**

Data and statistical code will be made openly available through the UCL data repository, subject to the ability to remove personally identifiable information. Data will be deposited with UCL research data repository (<https://www.ucl.ac.uk/library/research-support/research-data-management/ucl-research-data-repository>), where it will be given a Digital Object Identifier (DOI). The DOI will be cited in project reports and journal publications through a Data Access Statement or citation list. Metadata will also be made available to 3rd party research catalogues, such as <https://datamed.org/>. Qualitative responses will not be uploaded to this repository due to the potential to identify participants.

Anonymised data will be made openly available using a permissive licence, such as Creative Commons Attribution (CC-BY). If complete anonymity cannot be provided, it will be made available through a controlled access system. If data must be made available via controlled access, interested parties will be asked to provide information on their research (purpose, institutional affiliation, ethics approval) and sign a data sharing agreement indicating they will comply with the consent form and will not attempt to re-identify individuals. Access requests will be evaluated by the project team in the first instance. In cases where an access request is denied and the requester wishes to appeal, the request will be escalated to the UCL Research Governance Committee for consideration.

**Oversight and monitoring**

**Composition of the coordinating centre and trial steering committee {5d}**

There is no formal committee for the coordination and oversight of this trial. The PI will oversee and coordinate all aspects of the trial with the support of the project’s researchers. All decisions impacting the project protocol will be discussed with the lead researchers. The Advisory Group made up of experts internal (project staff from UCL and local partners (Ministry of Health of Senegal through DLSI and ANCS) will be consulted at key decision points.

**Data monitoring {21a}**

There is no formal committee for monitoring data collected as part of the project. Data monitoring will be undertaken by a researcher supervised by the PI. Questionnaire responses will be checked daily to determine any problems with the data collection instruments.

**Adverse event reporting and harms {22}**

An adverse event will be defined as a participant becoming significantly distressed as a consequence of their involvement in the trial. All adverse events, as a consequence of participation in the study, occurring after the entry into the study and until the end of the study will be recorded and will be treated on a case-by-case basis. In the event of an unanticipated adverse event that may cause direct harm or threat to the participants or others that are related to study implementation, the local staff will notify the PI. Per protocol, an unanticipated event report will be submitted promptly to the Senegal National Ethics Committee and the UCL ethics committee.

During the study, we might have some minor adverse events such as syncope during blood drawing for laboratory testing. Patients will be informed of this risk. Laboratory technicians will be trained on how to deal with these minor events. An unlikely adverse event could be an infection at the site of the needle prick, the chance of which will be minimized through observing international standards of blood sample collection. The respondent will be properly counselled on how, where and when to seek treatment in case of such an incident. The use of PrEP will be closely monitored by medical doctors involved in the PrEP rolled out in Senegal.

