**Criteria for discontinuing or modifying allocated interventions {11b}**

All adverse events will be treated on a case-by-case basis. In the event of an unanticipated adverse event that may cause direct harm or threat to the participants or others that are related to study implementation. An unanticipated event report will be submitted promptly to the Senegal National Ethics Committee and the UCL ethics committee per protocol.

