**Provisions for post-trial care {30}**

Any participants who suffer harm, e.g., psychological distress, as a consequence of the trial will be supported by the relevant CBO's psychological support services. Those in the control group, that remain in the study until the end of the project, will receive the same intervention at the end of the trial

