**Frequency and plans for auditing trial conduct {23}**

The PI meets weekly with researchers conducting the daily activities of the trial online to discuss and review trial progress, and at least monthly with the full investigator team. Any adverse events or issues in trial progress will be promptly communicated with the investigator team at these meetings or between meetings if necessary. Progress to the trial funder will be reported annually. Any trial protocol amendments will be reported to the University College London Research Ethics Committee and National Ethics Committee in Senegal.

**Plans for communicating important protocol amendments to relevant parties (e.g., trial participants, ethical committees) {25}**

Any amendments to the protocol will be provided to the University College London Research Ethics Committee and National Ethics Committee in Senegal.

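### The adverse-event definition covers only significant distress, conflicts with the physical examples in its own section, and leaves out reactions to PrEP

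*Protocol*

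**What the plan says.** The protocol section Adverse event reporting and harms {22} opens with a definition: "An adverse event will be defined as a participant becoming significantly distressed as a consequence of their involvement in the trial". Its recording rule covers all adverse events that result from participation; those from study entry "until the end of the study will be recorded and will be treated on a case-by-case basis". The second paragraph of the section says "we might have some minor adverse events such as syncope during blood drawing for laboratory testing" and "An unlikely adverse event could be an infection at the site of the needle prick", and describes how each is to be handled. Its only sentence on the study drug is "The use of PrEP will be closely monitored by medical doctors involved in the PrEP rolled out in Senegal".

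Three other sections bear on the point:

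- Criteria for discontinuing or modifying allocated interventions {11b} sets out the ethics-committee report, which applies "In the event of an unanticipated adverse event that may cause direct harm or threat to the participants or others" where the event relates to study implementation.
- Frequency and plans for auditing trial conduct {23} says "Any adverse events or issues in trial progress will be promptly communicated with the investigator team".
- Provisions for post-trial care {30} refers to "Any participants who suffer harm, e.g., psychological distress, as a consequence of the trial", so there distress is only one example of harm.

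The trial compares PrEP with nothing {6b}. None of the primary or secondary outcomes listed under {12} is a PrEP side effect.

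**The concern.** A harms section has to tell field staff what to write down. This one gives a definition that excludes physical events and then names two physical events as adverse events. Staff can work out that those two count, because they are named. They cannot work out the same for a reaction to PrEP, which appears in neither place although PrEP is what participants are randomised to.

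The safety record is what is at stake. If PrEP reactions without marked distress are never required to be logged, a low adverse-event count says little about the drug's tolerability in these women, and a reader of the results would have no means of knowing that.

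**Working it through.** The protocol gives no figure to reproduce here. The check sets the provisions side by side and asks whether each would bring into the trial record an expected PrEP reaction in a woman who is not markedly distressed.

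| Protocol section | What it covers | Captures such a reaction? |
|---|---|---|
| {22} definition | Significant distress caused by trial involvement | No |
| {22} examples | Fainting at blood draw; needle-site infection | No; both concern blood sampling |
| {22} recording rule | All adverse events, the defined term | Not if the definition is applied |
| {22} doctors' monitoring | PrEP use | No event to record and no route to the trial is stated |
| {11b} and {22} ethics report | Unanticipated adverse events related to study implementation | No; an expected reaction is not unanticipated |
| {23} escalation | Adverse events, and issues in trial progress | The first limb uses the defined term; the second is an item for team communication, not an event record |
| {11c} peer leaders | Problems passed to the research team | A channel for concerns, with no recording rule |
| {5d} Advisory Group | Includes the Ministry of Health; consulted at key decisions | Not an event record |
| {18a} survey | Includes health status | No PrEP-reaction item is stated |
| {21a} data monitoring | Daily check of questionnaire responses; no formal committee | Aimed at problems with the instruments |

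No row requires the reaction to be recorded. Programme records cannot be assumed to fill the gap, because {12} reports limited access to health-system information even on who received PrEP.

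The protocol does bound the group concerned and the time window.

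- **Women who could be offered PrEP before the survey.** 500 randomised 3:2 gives 500 × 3/5 = 300 treatment and 500 × 2/5 = 200 control. The upper bound is therefore 300. Actual exposure is lower, because {11a} provides for refusals and for women found ineligible at screening.
- **Time from approach to survey.** Treatment-arm women were approached from October 2021 to January 2022 {11a}, and the survey ran in April and May 2022 {12}. Days of the month are not given, so the bounds use month ends.
  - Shortest: 31 January to 1 April 2022 = 28 + 31 + 1 = 60 days, about 2 months.
  - Longest: 1 October 2021 to 31 May 2022 = 31 + 30 + 31 + 31 + 28 + 31 + 30 + 30 = 242 days, about 8 months.
  - Time on PrEP may be shorter, because screening comes after approach.

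No count of missed events can be computed without uptake and reaction risk, and the protocol states neither.

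**The case against.** The best defence is that the definition is one loosely drafted sentence. The examples in {22} are introduced as an open list, and {30} treats distress as an example only, so the authors plainly use the term more broadly. On that reading the recording rule, which covers all adverse events resulting from participation, could reach a PrEP reaction too. PrEP was delivered by the Ministry of Health and its partner organisation {9}, its clinical monitoring is assigned to rollout doctors, and the objectives {7} concern condom use, so leaving out a side-effect outcome is a choice of scope. Peer leaders relay problems, including those about the intervention {11c}. No comparison of adverse events by arm is planned. Much of the protocol is also in the past tense, so rewording may come too late to recover events.

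Several of these points stand. Delegating clinical care is reasonable, the scope choice is legitimate, a sensible clinician might report a serious reaction anyway, and completed follow-up would limit the remedy. They do not remove the problem. The broad reading has to be inferred against a sentence that expressly defines the term, and even then nothing names PrEP reactions or says how the rollout doctors pass them to the trial. The 300-woman bound also stops at the survey. Controls were offered PrEP afterwards, so if the recording period extends past that point, the group concerned is larger.

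**Conclusion.** The concern holds. As written, the definition contradicts its own section, and taken literally it leaves an expected PrEP reaction without marked distress outside the recording rule, the ethics report and the adverse-event limb of team escalation.

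The size is minor and confined to the safety record; the primary analysis of condom use and its perceived necessity is unaffected. The group concerned before the survey is at most 300 of 500 women, with 60 to 242 days between approach and survey, on the assumption that approaches and interviews could fall on any day of the stated months. The conclusion rests on applying the stated definition wherever the protocol uses the term. Staff who read it more broadly may have recorded more than the text requires, but the protocol gives no assurance that they did.

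**What to change.** Replace the definition in {22} with one covering any physical or psychological harm arising from trial participation, explicitly including specimen collection and PrEP use, with events recorded by arm. Use the same definition in {11b} and {23}. Add one line requiring the rollout doctors to notify the principal investigator of PrEP reactions in trial participants.

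If follow-up is complete, new wording cannot recover past events. In that case, request the programme's safety records where access allows, and state in the results that the adverse-event count does not establish absence of PrEP reactions.

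The cost is protocol wording, one notification line, a few more events to log and, if needed, a records request whose yield may be incomplete.

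A separate small correction, which carries no weight in the above: sections {26b} and {11a} pair liver function with creatinine, which is a kidney test. This is probably a wording slip, with no effect on eligibility shown; the responsible clinicians should correct the organ or the test.

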**Frequency and plans for auditing trial conduct {23}**

The PI meets weekly with researchers conducting the daily activities of the trial online to discuss and review trial progress, and at least monthly with the full investigator team. Any adverse events or issues in trial progress will be promptly communicated with the investigator team at these meetings or between meetings if necessary. Progress to the trial funder will be reported annually. Any trial protocol amendments will be reported to the University College London Research Ethics Committee and National Ethics Committee in Senegal.

**Plans for communicating important protocol amendments to relevant parties (e.g., trial participants, ethical committees) {25}**

Any amendments to the protocol will be provided to the University College London Research Ethics Committee and National Ethics Committee in Senegal.

**Dissemination plans {31a}**

The project partners ANCS and the Ministry of Health in Senegal, and the funders will be provided with a summary of the findings of the trial. The findings will also be reported in high-impact scientific journal articles and presented at scientific national and international conferences and in public forums as requested.

A policy brief will also be disseminated by those stakeholders through internal newsletters.

**Abbreviations**

- PrEP – Pre-exposure prophylaxis
- ANCS – Alliance Nationale des communautes pour la sante
- DLSI – Division de lutte contre le SIDA et les IST, Ministère de la sante du Senegal
- UCL – University College London
- DSH – Data Safe Haven
- CBO – Community-based organisation
- STI – Sexually transmitted infection
- HIV – Human immunodeficiency virus
- CEO – Chief Executive Officer
- PI – Principal investigator
- UKRI – UK Research and Innovation Council

**Declarations**

**Acknowledgements**

We would like to say thank study participants.

**Funding {4}**

This project is funded by a MRC grant awarded to [name] [name] MR/T00262X/1 and a grant from Erasmus university. UKRI has no role in the design or conduct of the study or the interpretation and dissemination of the findings. UKRI may be contacted at [[contact]](mailto:[contact]) or <https://www.ukri.org/about-us/contact-us/>.

**Availability of data and material {29}**

The team at UCL and Erasmus will have access to the final dataset, held on the DSH at UCL. The data will be available on the UCL repository at the time of publication of the trial results.

**Consent for publication {32}**

Not applicable.

**Competing interests {28}**

The authors declare that they have no competing interests.

